#### C. Documentation of clinical course and outcome

- To document the (successive) antimicrobial and adjunctive treatments administered and reasons for any interruption or change
- To observe whether the treatments are administered according to the supervised ITM's state-of-the-art and document the reasons for deviation
- To document the follow-up strategy in the real-life (frequency of visits, monitoring...)
- To determine the proportion of documented microbiological cure, in addition to the defined clinical cure (or stabilization/non-progression)

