## 5. METHODOLOGY

### 5.1. REGISTER DESIGN

For this national and international multicentric effort, REDCap (Research Electronic Data Capture) will be used to offer harmonized disease-specific case report form (CRF), as well as state-of-the-art recommendations. REDCap is a GCP-compliant web-based metadata open-source software program available to academic institutional partners of Vanderbilt University. It protects data with secure web authentication, data logging and Secure Sockets Layer (SSL) encryption, and has features specifically designed for registry data management, including (i) customizable data collection forms, (ii) data validation and quality control checks, (iii) advanced reporting and export capabilities and iv) audit trails for tracking changes to data.

The Tropistry REDCap-based registers (one for each selected tropical disease) are being constructed to collect relevant demographic, diagnostic and clinical data using a predefined core dataset (Section 6.5 for full details). It is designed as a registry to harmonize as much as possible the selection of treatments (based on state-of-the-art review and expert advice) and suggested follow-up. Recruitment will include all patients diagnosed with one of the target diseases (see case definitions for each of them), either a treatment has to be initiated or not. Data will be entered directly into REDCap by an investigator from each participating site. Data will be stored pseudonymously at ITM.

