  - Administered antiparasitic and adjunctive treatment (in case different of recommended, request to explain the reason for deviation)
  - Description and timing of drug-related adverse event if any

- Need of treatment interruption and reason (availability, adverse event, disease progression...)
- Laboratory changes (Electrolytes, Creatinine, liver function panel, Platelet count, red blood cell count, hemoglobin, white blood cell count, neutrophils, leukocytes, eosinophil count)
- Frequency and timing of follow-up visits with specific findings, if any
- Treatment response regarding clinical features (disease progression vs. stabilization vs. cure), with day of assessment
- Treatment response regarding microbiological outcome: eradication, reduction of the parasitic load, with day of assessment
- If inpatient stay: days on normal ward, intermediate care, intensive care unit total, as a marker of morbidity
- In case of death, cause of death
- Additional information on the case can be entered as a narrative

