## 5.6. STATISTICAL ANALYSIS

The international register will be analyzed annually to produce descriptive statistics on different variables including patient safety, patient demographics, details on diagnosis and administered treatments. Clinical outcomes and the follow-up of patients will also be assessed. Association between specific treatment strategies and patient safety/patient-related parameters will be analyzed using analysis of variance or Student's t-test for the continuous variables (or equivalent non-parametric tests for non-normally distributed variables Mann–Whitney U test or Kruskal-Wallis test) and the chi-square tests or Fisher's exact test for the categorical variables as well as multivariable regressions. Time to event analysis, by using Kaplan-Meier and Cox proportional hazard models will be performed to examine factors associated with the clinical outcomes. All statistical analyses will be performed using STATA, Python, and/or R statistic software and will be performed by trained personnel (epidemiologist, statistician) using current methods of analysis.

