### 7.1.PRIVACY CONSIDERATIONS

The following measures will be taken to rule out risk of re-identification for patients registered in Tropistry :

1. The dataset of the international register will not contain any directly identifying information, i.e., no name, birth date, place of residence (just country of residence), insurance company or any identifiers linked to the patient record at the participating center.
2. No specific dates will be encoded. The day of initial diagnosis will remain unknown to the register, only the year will be specified. All major events will be recorded as days from diagnostic ascertainment (day 0)
3. Almost all data will be collected in categories, e.g. age groups, lab values etc., making it almost impossible to link the data with other sources, e.g., by performing a reverse database search in the hospital information system.
4. All text items will be screened for potentially identifying information. Accidental breaches of anonymity will be reported to the responsible investigator and permanently deleted from the database. Relevant and shareable information will be moved into a structured data item.

Taking these considerations into account, the risk of a full data breach can be considered very low. Tropistry will be maintained in the ITM REDCap server. For data clearance and optimization pipelines as well as complete analyses of the uncensored dataset, the full dataset may be moved to certified secure network areas. Such processing and analysis will be performed by a small group of authorized persons supervised by the principal coordinating investigator. All data will be stored for at least 10 years following the end of the registry (in case of termination).

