Follow-up, treatment failure, and scarring assessment have been standardized in the registry following recent international recommendations. Clinical response is now evaluated at predefined time points: Day 42 and Day 90 (initial cure assessments), 6 months (final cure), and optionally at 9–12 months to detect relapse (see Figure). Treatment failure is defined as <50% re-epithelialization or flattening by Day 42, or <100% re-epithelialization or flattening by Day 90, in line with the consensus reached in harmonized clinical trial methodologies for cutaneous leishmaniasis. In addition, scar outcomes are systematically assessed using a standardized grading (from no visible scar to severe disfigurement or functional limitation) and classified by type (e.g. flat, atrophic, hypertrophic, keloid, pigmentary alteration). This approach enhances comparability across sites and aligns with WHO/TDR and DNDi guidance for clinical evaluation of CL.

[figure not shown]

Based on Olliaro P et al. Harmonized clinical trial methodologies for localized cutaneous leishmaniasis and potential for extensive network with capacities for clinical evaluation. PLoS Negl Trop Dis 2018 12(1): e0006141.

As already highlighted, the purpose is to make Tropistry as accessible as possible for busy clinicians confronted with any of the target diseases. For pragmatic reasons, inclusion and data entry will be retrospective (with reasonable delay of maximum 6 months after initial diagnosis), and considered as secondary use of clinical data for institutions where an optout strategy is in place. In other settings, a formal written informed consent will be requested for each included patient.

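### Outside the leishmaniasis module, cure is dated by the visit at which it was seen and no common visit days are set, so the planned Kaplan-Meier and Cox analyses can pick up visit spacing as a treatment effect

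*Protocol*

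**What the plan says.** Protocol 5.5 dates clinical response by the visit: "Treatment response regarding clinical features (disease progression vs. stabilization vs. cure), with day of assessment". Microbiological response is handled in the same way: "Treatment response regarding microbiological outcome: eradication, reduction of the parasitic load, with day of assessment". Section 7.1 sets the clock: "All major events will be recorded as days from diagnostic ascertainment (day 0"). The core list asks for no separate day of cure onset and no last day known not to be cured. It does ask for "Frequency and timing of follow-up visits with specific findings, if any".

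The core text fixes no visit days. Section 5.1 describes a registry meant "to harmonize as much as possible the selection of treatments (based on state-of-the-art review and expert advice) and suggested follow-up", so follow-up is advised and not required. Section 4.2 C makes visit frequency something to observe: "To document the follow-up strategy in the real-life (frequency of visits, monitoring"...). Section 8, on acute schistosomiasis, names no response assessment days and allows each centre its own regimen.

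Section 9, on cutaneous and mucocutaneous leishmaniasis, differs: "Clinical response is now evaluated at predefined time points: Day 42 and Day 90 (initial cure assessments), 6 months (final cure"), with an optional later visit for relapse.

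On analysis, Section 5.6 states: "Time to event analysis, by using Kaplan-Meier and Cox proportional hazard models will be performed to examine factors associated with the clinical outcomes". The Protocol Summary repeats this in similar terms. Section 4.1 defines clinical effectiveness as a rate of cure or stabilisation at a suitable timepoint.

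**The concern.** A patient who heals between two visits is counted as cured at the second. The true cure time lies in an interval, and its right-hand end is entered as if exact. Standard Kaplan-Meier and Cox methods take that day at face value.

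If everyone is seen on the same days, all groups are delayed alike and a comparison stays fair. If one treatment's patients are seen less often, their cures are recorded later and that treatment appears slower. In this registry the centre can drive both the regimen and the visit spacing, so the two may be linked. Acute schistosomiasis is especially exposed because Section 8 puts spontaneous recovery at 2 to 10 weeks (14 to 70 days), a period in which visit gaps of several weeks are large relative to the event time.

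At stake is any reading of the annual time-to-event results as showing that one regimen cures faster, in a registry whose output is meant to feed treatment recommendations.

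**Working it through.** The plan gives no effect size, error rate, event count or sample size calculation, so it has no figure to reproduce. The check asks how large the bias is when the treatments are truly equal.

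**Inputs from the protocol.** At least 100 inclusions per disease (5.3), taken as 50 per group. Recovery over 14 to 70 days (Section 8). Leishmaniasis assessments at days 42, 90 and about 182 (Section 9).

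**Assumptions not in the protocol.** Exponential time to cure, the same in both groups, with a median of 28 to 60 days. Visit gaps of 14 to 30 days in one group and 28 to 60 in the other. Cure recorded at the first visit on or after true cure.

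**Step 1: the delay in closed form.** With rate λ = ln 2 / median and visit gap d, the mean recorded time, ignoring end of follow-up, is d / (1 − exp(−λd)). The true mean is 1/λ.
- Median 28 days: the true mean is 28/0.693 = 40.4 days. For d = 14 the recorded mean is 14/(1 − 0.707) = 47.8. For d = 42 it is 42/(1 − 0.354) = 65.0. The delays are 7.4 and 24.6 days.
- Median 60 days: the true mean is 86.6 days. For d = 14 the recorded mean is 14/(1 − 0.851) = 93.8, and for d = 28 it is 28/(1 − 0.724) = 101.3. The delays are 7.2 and 14.8 days.

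The distortion grows as the gap lengthens relative to healing time.

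**Step 2: the Cox model, spacing fully separated by treatment.** There were 600 simulated registries per row, with Efron ties and a two-sided 5% test. The HR is for cure in the less often seen group, and the true value is 1. Follow-up is 182 days, except in the rows marked *, where it is 365.

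| Median (days) | Visit gaps (days) | HR | p < 0.05 |
|---|---|---|---|
| 28 | 14 vs 14 | 1.00 | 4.5% |
| 28 | 14 vs 28 | 0.82 | 17% |
| 28 | 14 vs 42 | 0.67 | 48% |
| 42 | 14 vs 28 | 0.88 | 8% |
| 42 | 14 vs 42 | 0.78 | 23% |
| 45* | 14 vs 42 | 0.79 | 22% |
| 60 | 14 vs 28 | 0.93 | 5.5% |
| 60 | 14 vs 42 | 0.85 | 11% |
| 60* | 30 vs 60 | 0.82 | 15% to 18% |

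The median-28, 14 vs 42 row gave 48% to 51% across repeat runs.

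**Step 3: spacing only associated with treatment.** Here 75% of one group and 25% of the other have the long gap. For 14 vs 42 days the HR is 0.82 with 15% rejection at median 28, and 0.88 with 9% at median 45. For 30 vs 60 days at median 60 it is 0.91 with 9%. Across repeat runs the range is 0.79 to 0.95 with 5% to 20%. At 65/35, rejection is about 4% to 8%.

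**Step 4: a common schedule.** With days 42, 90 and 182 in both groups, the HR is 0.99 with 4.2% rejection (median 42) and 0.99 with 5.5% (median 60).

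**Step 5: the proportion cured by about six months.** In the 182-day rows of Step 2 the largest difference is 87.8% vs 86.1%, or 1.7 points (median 60, 14 vs 28 days). It arises because the last 14-day visit falls on day 13 × 14 = 182 and the last 28-day visit on day 6 × 28 = 168.

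**Step 6: the remedy.** An interval-censored model on full-separation data gave an HR of 0.99 to 1.01, with rejection at or near nominal (3% to 10% across runs).

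**The case against.** The strongest reply is that the protocol does not rest effectiveness on these models. The primary measure is a rate at a timepoint, and the Protocol Summary assigns associations between treatment and effectiveness to group tests and multivariable regression. Kaplan-Meier and Cox come in a separate sentence about factors associated with outcomes. This stands, and it limits the point to the time-to-event analyses. It does not remove the point, because treatment is an obvious factor to enter in such a model.

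Second, nothing in the documents says that any regimen is followed more closely than another. This also stands: the bias is conditional, and its size depends on assumed gaps. Full separation is the upper end, and with mild differences little remains.

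Third, interval censoring is a detail for the SAP, and Annexes 2 and 4, which list the data, are not in the text at hand. In part this is fair. But the protocol itself names both the event date and the method, and the two fit poorly. That is a choice made, not a detail left open.

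Two stronger readings are tempting. A reader might infer that visit frequency is left to each centre throughout, or that the three leishmaniasis visit days add a bias by piling up events. The documents do not support either: Section 9 sets common assessment days, and under them Step 4 shows no bias. Ties alone do not shift the hazard ratio. Actual visits may drift from those days, but the text gives no measure of that. A reader might also infer that the primary result is compromised. Step 5 shows that it is little affected at about six months.

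**Conclusion.** The point holds for acute schistosomiasis, and for any later disease module that sets no common assessment days. It is confined to time-to-event comparisons of cure. If spacing is fully separated by treatment, the HR is about 0.67 to 0.93 with 5% to 50% false positives over the scenarios tested. At a 75/25 association it is about 0.79 to 0.95 with 5% to 20%. If spacing is unrelated to treatment, there is no bias.

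These figures assume exponential healing, 50 patients per group and the visit gaps stated. The protocol supplies only the recovery range, the expected 100 inclusions and the leishmaniasis schedule. The point is worth acting on because the change is cheap and the visit-level data are best secured before records accumulate. It does not call the primary objective into question.

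**What to change.** - **Section 5.6:** base the effectiveness comparison on the proportion cured at a common assessment window for each disease, in line with Section 4.1. Leishmaniasis already has its days. Acute schistosomiasis needs an analysis window stated.
- **Section 5.6:** where time to cure is wanted, analyse it as interval-censored, from the last visit not cured to the first visit cured, in place of standard Kaplan-Meier and Cox.
- **Section 5.5:** record response status at every documented visit, including not yet cured. The present item covers visit timing with findings only where there are any, and Section 5.4 allows entry once the case is complete, so the left end of the interval is not assured.

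The cost is a change of wording, slightly wider confidence intervals and at most one repeated CRF field. Standard R and Stata routines cover the analysis.

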## 5.6. STATISTICAL ANALYSIS

The international register will be analyzed annually to produce descriptive statistics on different variables including patient safety, patient demographics, details on diagnosis and administered treatments. Clinical outcomes and the follow-up of patients will also be assessed. Association between specific treatment strategies and patient safety/patient-related parameters will be analyzed using analysis of variance or Student's t-test for the continuous variables (or equivalent non-parametric tests for non-normally distributed variables Mann–Whitney U test or Kruskal-Wallis test) and the chi-square tests or Fisher's exact test for the categorical variables as well as multivariable regressions. Time to event analysis, by using Kaplan-Meier and Cox proportional hazard models will be performed to examine factors associated with the clinical outcomes. All statistical analyses will be performed using STATA, Python, and/or R statistic software and will be performed by trained personnel (epidemiologist, statistician) using current methods of analysis.

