| Register Duration   | 
Registry start date: 10/2024
 
Registry end date: none
                                                                                                                                                                                                                                                                                                                                                                                                                                                                                                                                                                                                                                                                                                                                                                                                                                                                                                                                                          |
| Statistical Methods | 
The REDCap database will be analyzed on annual basis to statistically describe different variables as patient demographics, baseline clinical presentation, methods of diagnosis, staging of disease, (recommended) treatments, frequency and pattern of adverse events, complications and clinical outcome. Deviations with suggested treatments will also be captured (as well as reasons for alternative decisions). Association between specific treatment strategies and patient safety/clinical effectiveness will be analyzed using analysis of variance or Student's t-test for the continuous variables (or equivalent non-parametric tests for non-normally distributed variables Mann–Whitney U test or Kruskal-Wallis test) and the chi-square tests or Fisher's exact test for the categorical variables as well as multivariable regressions. Time to event analysis, by using Kaplan-Meier and Cox proportional hazard models will be performed to examine factors associated with specific outcomes.
 |

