These “recommendations” will of course evolve with the scientific advances and new knowledge (included that generated by Tropistry). It is important to highlight that each center may propose different therapeutic regimens, according to local/national guidelines. As of June 2024, based on the experience at ITM (current state-of-the-art at ITM; manuscript about a recent cluster being submitted), we will recommend in Tropistry the following therapeutic approach:

- In case of symptomatic acute schistosomiasis,
  - If diagnosis earlier than 6 weeks after exposure/infection: only methylprednisolone 0.5 mg/kg/day for 3 days, to be prolonged/repeated if unsatisfactory control of inflammatory symptoms
  - If diagnosis made later than 6 weeks after infection: praziquantel 40 mg/kg single dose, followed after 2-4 hours by methylprednisolone 0.5 mg/kg/day for 3 days, to be prolonged/repeated if unsatisfactory control of inflammatory symptoms (note that this interval allows the concentration peak of praziquantel within 1-2 hours after administration, with no drug interaction)

- In case of asymptomatic acute schistosomiasis (for example within a cluster of cases)
  - Diagnosis earlier than 6 weeks after infection: abstention
  - Diagnosis later than 6 weeks after infection: praziquantel 40 mg/kg single dose followed after 2-4 hours by methylprednisolone (to prevent any clinical exacerbation)

All patients with acute schistosomiasis (either symptomatic or not) will receive a second 40 mg/kg single-dose course of praziquantel at week 12 after infection (to clear all juvenile worms which have meanwhile become adults). Here there is a large consensus between experts.

As already highlighted, the purpose is to make Tropistry as accessible as possible for busy clinicians confronted with any of the target diseases. For pragmatic reasons, inclusion and data entry will be retrospective (with reasonable delay of 6 months after initial diagnosis), and considered as secondary use of clinical data for institutions where an optout strategy is in place. This will be the case with most partners for this first phase of the project focusing on acute schistosomiasis. In other settings, a formal written informed consent will be requested for each included patient.

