| Mucosal involvement        | Yes                                                         | Yes                                             | Yes                                              |
| Immunosuppression          | Yes                                                         | Yes                                             | Yes                                              |
| Failure to local treatment | Yes                                                         | Yes                                             | Yes                                              |
| DCL/LR                     | Yes                                                         | Unclear                                         | Yes                                              |

|                      |         |         |         |
|----------------------|---------|---------|---------|
| Subcutaneous nodules | Yes     | Unclear | Yes     |
| Lymphatic spread     | Yes     | Yes     | Yes     |
| Infection in Bolivia | Unclear | Yes     | Unclear |

DCL: diffuse cutaneous leishmaniasis, LR: Leishmania recidivans

aFor the IDSA guidelines there are cases where the simple and complex is not mutually exclusive; e.g. 1-4 cm size, and 2-4 lesions

bA distinction is made between Old-World species (with the addition of *L. mexicana* from the New-World), for which more than 3 lesions are considered to be complex, while for New-World species (with the exception of *L. mexicana*) having multiple lesions is sufficient to qualify as complex cutaneous leishmaniasis.

In general, for simple CL, observation/simple wound care or local treatment are sufficient, while systemic therapy should be considered for complex CL. Of note there are still slight differences between guidelines about some criteria (especially regarding the size and number of lesions) but treatment decisions based on "common sense" will be suggested whenever discrepancies occur. In all cases, confirmation of the diagnosis is important, and whenever feasible, PCR-based species identification will be recommended because it increasingly guides therapy choices. However, species typing might not be available everywhere; in such cases, clinical judgment and knowledge of the probable region of infection will guide management.

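### Crude tests and unspecified regressions stand side by side for treatment comparisons, although the protocol's own guidance ties treatment to prognosis; say which result is to be interpreted

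*Protocol*

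**What the plan says.** **The analysis.** Protocol Section 5.6 says: "Association between specific treatment strategies and patient safety/patient-related parameters will be analyzed using analysis of variance", with t-test or rank-based alternatives for continuous variables and chi-square or Fisher's exact test "for the categorical variables as well as multivariable regressions". It adds Kaplan-Meier methods, and "Cox proportional hazard models will be performed to examine factors associated with the clinical outcomes". The summary in Section 2 has the same list but names effectiveness: "Association between specific treatment strategies and patient safety/clinical effectiveness will be analyzed using analysis of variance". Neither place says whether the crude or the adjusted result is the one to interpret.

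**The treatment guidance.** For acute schistosomiasis, Section 8 divides cases at six weeks after infection and by symptoms. For early symptomatic cases: "If diagnosis earlier than 6 weeks after exposure/infection: only methylprednisolone". For early asymptomatic cases: "Diagnosis earlier than 6 weeks after infection: abstention". Later cases, with or without symptoms, are advised praziquantel followed by a steroid. For leishmaniasis, Section 9 says: "In general, for simple CL, observation/simple wound care or local treatment are sufficient, while systemic therapy should be considered for complex CL". It also names species and host immunity as grounds for the choice.

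**The use of results.** Section 2 wants the analyses to support therapeutic recommendations, Section 3 wants them to help identify the best practices, and Section 5.3 expects at least 100 inclusions per disease to suffice for clinical recommendations.

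**The concern.** When the features that decide treatment also predict outcome, a crude comparison of treatment groups compares kinds of patient as much as treatments. Here the protocol itself supplies the link. In the Section 9 table, complex leishmaniasis includes mucosal involvement, immunosuppression and failure of local treatment, so patients who did badly on local therapy are moved by definition towards systemic therapy. In Section 8, treatment groups differ in stage of infection from the outset.

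Sections 5.6 and 2 nevertheless give the crude tests the same standing as the regressions. An annual report that led with a chi-square of cure by treatment would follow the protocol as written. Sections 8 and 9 say that the recommendations will evolve with knowledge from the registry, so a confounded contrast could feed back into later advice.

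**Working it through.** The protocol has no figure to reproduce: Section 2 states that there is no sample size calculation. The check is therefore a reading of the text plus an illustration with assumed rates.

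**1. Size of the crude bias, leishmaniasis.**

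From the protocol: 100 patients (Section 5.3). Assumed: half simple and half complex disease; cure depends on complexity only, so the true treatment effect is zero; local therapy goes to most simple and few complex cases.

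| | Scenario A | Scenario B (milder) |
|---|---|---|
| Cure, simple / complex | 85% / 60% | 85% / 65% |
| Share given local therapy, simple / complex | 90% / 20% | 80% / 30% |
| Local group, simple + complex | 45 + 10 = 55 | 40 + 15 = 55 |
| Systemic group, simple + complex | 5 + 40 = 45 | 10 + 35 = 45 |

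Crude cure in a group = (simple patients × simple cure + complex patients × complex cure) / group size.

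- A, local: (45 × 0.85 + 10 × 0.60) / 55 = 44.25 / 55 = 80.5%.
- A, systemic: (5 × 0.85 + 40 × 0.60) / 45 = 28.25 / 45 = 62.8%. Difference 17.7 points.
- B, local: (40 × 0.85 + 15 × 0.65) / 55 = 43.75 / 55 = 79.5%.
- B, systemic: (10 × 0.85 + 35 × 0.65) / 45 = 31.25 / 45 = 69.4%. Difference 10.1 points.

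**2. How often the crude test would reject.**

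With pooled cure p, SE = √[p(1 − p)(1/55 + 1/45)], and the two-sided 5% rejection probability is about Φ(difference/SE − 1.96).

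- A: p = 72.5/100; SE = √(0.725 × 0.275 × 0.0404) = 0.090; ratio 1.97; about 50%.
- B: p = 75/100; SE = √(0.75 × 0.25 × 0.0404) = 0.087; ratio 1.16; about 21%.

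A simulation of 20,000 registries with an uncorrected chi-square gave mean differences of 17.6 and 10.1 points, with 51% and 22% rejection.

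**3. Sensitivity to the assumptions.**

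With 50 patients per treatment group and half of all patients severe, the share of mild / severe cases given the more intensive treatment was varied from 40% / 60% to 0% / 100%.

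- Cure 85% mild against 65% severe: spurious difference 4 to 20 points, rejection 7% to 64%.
- Cure 90% against 60%: 6 to 30 points, rejection 10% to 95%.

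**4. What adjustment can do.**

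In both scenarios cure is the same for local and systemic therapy within simple disease and within complex disease, so an estimate stratified by complexity is centred on zero. The price is precision. The share of treatment information left is roughly the within-stratum variance of treatment divided by its total variance (0.55 × 0.45 = 0.2475).

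- A: (0.5 × 0.9 × 0.1 + 0.5 × 0.2 × 0.8) / 0.2475 = 0.125 / 0.2475 = 51%.
- B: (0.5 × 0.8 × 0.2 + 0.5 × 0.3 × 0.7) / 0.2475 = 0.185 / 0.2475 = 75%.

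Across the range in step 3 the share falls from 96% to 84%, 64%, 36% and, at 0% / 100%, to 0%. At that end no adjustment of any kind can estimate a treatment effect.

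**5. Acute schistosomiasis.**

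The Section 8 guidance defines four cells: earlier or later than six weeks, with or without symptoms. It gives one approach per cell. If it were followed in every case, treatment would not vary within a cell and the information share would be 0%. Comparisons would then rest on departures from the guidance and on local regimens.

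**6. Whether the strata can be formed.**

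The core dataset in Section 5.5 lists staging, symptoms, comorbidity and immunosuppression. It does not explicitly list time since infection or species. Section 7.1 counts major events in days from diagnosis, not from exposure. The disease-specific data lists are in Annexes 2 and 4, which were not available for this review, so this needs confirmation.

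**The case against.** The strongest reply is that adjusted analysis is already planned: the sentence that lists the crude tests ends with multivariable regressions, and Cox models follow. A reader might infer that the protocol compares treatments by unadjusted tests alone, or that it names the wrong tests. The text does not support that. The illustration above never runs the planned regressions, and all its rates are assumed. This part of the reply stands in full.

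Second, the covariate list can wait for a statistical analysis plan. That is also right, and its absence is not the point made here. What remains is that the protocol itself, in two places, gives crude tests equal standing for a treatment question.

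Third, a reader might infer that treatments do not overlap and that regression therefore cannot help. The documents leave this open. The guidance is advisory; Sections 8 and 9 let centres use other regimens and describe wide variation in practice; and Section 5.1 admits patients treated since 2022, before the June 2024 recommendation. Against that, Section 5.1 also aims to harmonise the choice of treatment, and the more it succeeds, the less overlap there will be.

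Fourth, the protocol speaks of association, and its primary objective is to document. That crude differences will be read as treatment effects is an inference. The stated aim of therapeutic recommendations makes it a reasonable worry, not a fact.

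**Conclusion.** The point holds in a limited form. Sections 5.6 and 2 put crude tests and unspecified regressions side by side and do not say which to interpret, while Sections 8 and 9 link treatment to features likely to affect outcome. With no true effect, a crude comparison of 100 leishmaniasis patients could show roughly 10 to 18 points in favour of local therapy, significant in about one registry in five (milder scenario) to one in two. Other assumptions widen this to 4 to 30 points. These sizes rest on assumed cure rates, an even split of simple and complex disease and assumed channelling; none comes from the protocol. No size is given for acute schistosomiasis.

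The planned regressions could remove this bias if they include the channelling features and if treatments overlap within strata. The documents settle neither condition. This is an inexpensive improvement worth making, not a defect that invalidates the registry.

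**What to change.** Change the wording of Section 5.6 and of the statistical methods in Section 2:

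1. Label crude tests between treatments as descriptive only.
2. Base treatment comparisons on regression adjusted for, or stratified by, the features that steer treatment. For leishmaniasis: simple or complex disease, species (or Old/New World) and immune status. For acute schistosomiasis: earlier or later than six weeks after infection, and symptomatic or asymptomatic. First confirm that the case report forms capture these, time since infection in particular.
3. Tabulate treatment by stratum before any comparison. Where treatments do not overlap, do not present the contrast as a treatment comparison; the six-week line is an example if the guidance was followed.

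None of this alters the clinical guidance. The cost is a few sentences, plus a data item if time since infection or species turns out not to be collected. Adjusted or within-stratum estimates will be less precise than crude ones: in the two scenarios above they keep about 51% and 75% of the treatment information. With about 100 patients per disease, some contrasts may not be estimable at all, and the report should then say so.
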